#### Moderator Analysis

To guide future app refinements and deployment strategies, moderation analyses will assess which patient characteristics are associated with deriving greater benefit from using Connections. For each proposed moderator, a linear regression model will be built to predict abstinence days at 6 months, controlling for abstinence days at baseline. An interaction term will be added to the model which crosses the proposed moderator with intervention group. Significant interaction effects will be decomposed to understand the differences between subgroups. We will examine potential moderation by sex, race, ethnicity, age, stage of ALD, comorbidities, marital status, education, AUD treatment engagement, and AUD treatment confidence, intention, readiness, and importance rulers, as well as testing directional hypotheses for the proposed moderators. Notably, we predict that sex will largely moderate effects of Connections, with women benefiting more than men in the intervention arm. Moderator analyses are exploratory and are considered hypothesis-generating rather than confirmatory.

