### Outcomes

#### Primary Outcomes

The primary outcome is patient alcohol use, which is measured using the patient-reported timeline follow-back (TLFB) calendar method and will be reported as percent days abstinent (Table 1) [38]. Abstinence, number of days drinking, and number of drinks per drinking day will be captured in the patient surveys. The TLFB will be administered once a month for 6 months to all enrolled participants using REDCap (Research Electronic Data Capture; Vanderbilt University), a password-protected electronic data capturing tool hosted at the University of Wisconsin-Madison [39].

**Table 1 table1:** Study outcomes, proposed outcome mediators, and outcome measurements used. Each dimension is measured by a well-validated instrument (Measure) and collected either from a patient survey, CHESS server logs, or from patient and/or staff interviews (Source) at different time points of the study (Timing). The selected measures allow for control of factors that may differ between patients and may impact alcohol use. The implementation process will be assessed using qualitative methods via semistructured patient and staff interviews.

Dimension			Measure		Source		Timing

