**Secondary effectiveness outcomes**							
	Quality of life	PROMIS^a^ Global Health [40]		Patient survey		0, 3, 6 months	
	Depression	PHQ-8^b^ [41]		Patient survey		0, 3, 6 months	
	Anxiety	GAD-7^c^ [42]		Patient survey		0, 3, 6 months	
	Insomnia	Insomnia severity index [43]		Patient survey		0, 3, 6 months	
	Health care usage and engagement with alcohol-targeted interventions	Health care usage questionnaire		Patient survey		0, 3, 6 months	
	Drinking motivations	DMQ-A^d^ [44]		Patient survey		0, 3, 6 months	
	Alcohol risk assessment	AUDIT-10^e^ [45]		Patient survey		0, 6 months	
	Pain intensity and interference	PEG^f^ [46]		Patient survey		0, 3, 6 months	
	Relatedness (mediator)	CHESS^g^ Bonding Scale [47]		Patient survey		0, 3, 6 months	
	Competence (mediator)	DTCQ-8A^h^ [48]		Patient survey		0, 3, 6 months	
	Autonomous motivation (mediator)	TSRQ^i^ [49]		Patient survey		0, 3, 6 months	
	Primary moderator variables (sex, rural and/or nonrural, clinic site)	Sex, rural and/or nonrural, clinic site (multidisciplinary ALD^j^ vs general hepatology)		Patient survey		0 months	
	Secondary moderator variables (race, ethnicity, education level, age, marital status, ALD severity)	Adapted upstream risks screening tool (URST)		Patient survey		0 months	

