#### Power and Sample Size

The analysis assumes an intra-individual correlation coefficient of ρ=0.10 in alcohol abstinence days in the longitudinal mixed-effects model. With 7.5% loss to follow-up and a moderate effect size estimate of 0.3σ (using published effect sizes from prior CHESS platform studies) [50,51], the planned sample size of 298 participants (149 per randomization group) will have power ≥80% to detect a meaningful difference between randomization groups for the primary outcome of alcohol abstinent days.

The projected randomization of 298 participants is expected to be met due to the estimated recruitment pool of approximately 2361 patients with ALD across both sites. Of this total population, it is expected that approximately 690 patients will be part of the multidisciplinary ALD clinics. The randomization goal is less than 13% of the total estimated eligible population, which is likely a feasible recruitment rate based on prior studies led by members of the research team [52]. This feasibility is further supported by the recent pilot research recruitment rate of 11 out of 20 (55%) patients with ALD approached [53].

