### Data Analysis

#### Primary Analysis

To test the primary aim, alcohol consumption outcomes will be compared between the usual care condition and the usual care plus the Connections app condition, stratified by site and clinic type, and adjusting for baseline abstinence and risky drinking (AUDIT-10 score). The analysis will use an intent-to-treat paradigm and use longitudinal linear mixed-effects models. The analyses will test a group-by-time interaction on the outcomes. If the interaction is not significant, a main group effect will be examined. The analysis assesses direct treatment effects on patient outcomes over time. The research team will construct a longitudinal model of our outcome measures at baseline and at 3 and 6 months after randomization. To address potential incomplete data from individual subjects, the research team will also conduct a mixed-model analysis of repeated measures based on the general linear model with an assessment of various covariance structures (compound symmetric, autoregressive order one, and unstructured). Covariance structure selection will be based on Akaike’s information criterion and Schwarz’s Bayesian criterion [55,56]. Pairwise comparisons between treatment groups and specific treatment time contrast in the mixed model will be conducted to respond to between-group effects and time-based effects. To address issues of incomplete data, the research team plans to estimate treatment effects according to four approaches: intention-to-treat, as-treated, per-protocol, and complier-average causal effect. Secondary analyses (as-treated, per-protocol, CACE) will only be formally evaluated if the primary intention-to-treat outcome demonstrates a statistically significant effect. Details of these approaches are outlined in Little and Yau [57] and Jo [58]. Missing data patterns (eg, possible dropouts) will be established from the longitudinal data and will be used to adjust the longitudinal intervention analysis according to pattern-mixture modeling. The research team will also examine additional secondary hypotheses (Table 3).

**Table 3 table3:** Summary of secondary study hypotheses. Predicted relationships between intervention engagement, participant characteristics (sex and location), and clinical outcomes, including proposed mediating mechanisms, to be examined during quantitative analysis.

Variable	Description of hypothesis

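### The exploratory moderator tests regress month-6 abstinence alone on baseline abstinence, although the outcome is collected monthly and the primary analysis is a longitudinal mixed model; an interaction averaged over follow-up would be more precise and closer to the primary result

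*Protocol article*

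**What the plan says.** Under Moderator Analysis, the protocol article fixes both the model and the time point: "For each proposed moderator, a linear regression model will be built to predict abstinence days at 6 months, controlling for abstinence days at baseline". A term crossing the moderator with study arm is then added. Baseline abstinence is the only adjustment covariate named. The section closes by stating the status of these tests: "Moderator analyses are exploratory and are considered hypothesis-generating rather than confirmatory". Anticipated Findings again describes the Table 3 hypotheses as exploratory.

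The outcome itself is measured repeatedly. Primary Outcomes says: "The TLFB will be administered once a month for 6 months to all enrolled participants using REDCap".

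The Primary Analysis section is longitudinal: "The analysis will use an intent-to-treat paradigm and use longitudinal linear mixed-effects models". It is stratified by site and clinic type and adjusted for baseline abstinence and AUDIT-10. Group-by-time is tested first, and a main group effect is examined if that interaction is not significant. On time points it says: "The research team will construct a longitudinal model of our outcome measures at baseline and at 3 and 6 months after randomization". Pattern-mixture methods are mentioned for that analysis only: they "will be used to adjust the longitudinal intervention analysis according to pattern-mixture modeling".

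Table 1 ranks sex, rurality and clinic type as the primary moderators, and Table 3 gives each a predicted direction.

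**The concern.** A moderator analysis should say for whom the reported treatment effect is larger or smaller. Here the moderator model differs from the primary model in form, time frame and named covariates, and no reason is given. The article could end up reporting a group effect over follow-up beside moderator results for a single 30-day window at the end.

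Interactions are also the least precise estimates that a trial of this size produces. The results are meant to guide refinement and deployment of the app. Resting them on one monthly window when up to six are available makes it likelier that real differences between women and men, rural and nonrural patients, or clinic types are missed or estimated erratically.

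**Working it through.** **Inputs from the protocol article (Power and Sample Size).** 298 participants, 149 per arm; 7.5% loss; effect 0.3 SD; within-person correlation 0.10, stated as: "The analysis assumes an intra-individual correlation coefficient of ρ=0.10 in alcohol abstinence days in the longitudinal mixed-effects model". The multidisciplinary clinics hold 690 of 2361 patients in the recruitment pool, or 29%.

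**Assumptions.** Two-sided alpha 0.05 (the article states no alpha); equal correlation between all months; an interaction of the same size in every month; correlations of 0.5 and 0.7 as alternatives to the plan's 0.10.

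**The plan's own figure.** With 149 × 0.925 = 137.8 per arm and variance (1 + (m − 1)ρ)/m for the mean of m follow-ups at ρ = 0.10, two-sided power for 0.3 SD is 70.2% for m = 1, 91.9% for m = 2 and 99.9% for m = 6. One-sided with m = 1 it is 80.1%. The stated power of at least 80% therefore holds on any repeated-measures reading. No power is stated for interactions.

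**Variance by target.** Adjusted for baseline, the variance of the mean of m follow-ups is V = (1 + (m − 1)ρ)/m − ρ².

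| ρ | V, month 6 | V, months 3 and 6 | V, months 1–6 | Month 6 ÷ months 3 and 6 | Month 6 ÷ months 1–6 |
|---|---|---|---|---|---|
| 0.10 | 0.990 | 0.540 | 0.240 | 1.83 | 4.1 |
| 0.50 | 0.750 | 0.500 | 0.333 | 1.50 | 2.25 |
| 0.70 | 0.510 | 0.360 | 0.260 | 1.42 | 1.96 |

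Both comparators are needed because Primary Analysis names months 3 and 6 while the calendar is collected monthly.

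**Interaction precision.** SE = √[V × (4/N) × (1/p + 1/(1 − p))], with N = 298 × 0.925 = 275.65 and p the share in one moderator group. For p = 0.5, ρ = 0.10 and month 6: √(0.990 × 16/275.65) = 0.240 SD. The interaction detectable with 80% power is 2.80 × SE = 0.67 SD. Each cell below gives that figure, then the power for an interaction of 0.3 SD (as large as the planned main effect).

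| Moderator split, ρ | Month 6 only | Months 3 and 6 | Months 1–6 |
|---|---|---|---|
| 50:50, 0.10 | 0.67 SD; 24% | 0.50 SD; 40% | 0.33 SD; 72% |
| 50:50, 0.50 | 0.58 SD; 30% | 0.48 SD; 42% | 0.39 SD; 58% |
| 50:50, 0.70 | 0.48 SD; 41% | 0.40 SD; 55% | 0.34 SD; 69% |
| 29:71 (clinic type), 0.10 | 0.74 SD; 21% | 0.55 SD; 34% | 0.36 SD; 64% |

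**Where the gain comes from.** Losing 7.5% of participants inflates an SE by 1/√0.925 = 1.04, about 4%. If month 6 remains the target, a mixed model using all months has 0.998 of the regression's variance at ρ = 0.10 and about 0.98 at ρ = 0.5 to 0.7. With an assumed 20% loss, the ratio is 0.94 to 0.996. Nearly all the gain is therefore due to averaging.

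**Sensitivity to a changing effect.** Averaging pays only if the mean interaction exceeds 1/√(variance ratio) of its month-6 value. For months 1–6 this is 1/√4.125 = 0.49 at ρ = 0.10, 1/√2.25 = 0.67 at ρ = 0.5 and 1/√1.96 = 0.71 at ρ = 0.7. An interaction rising in proportion to the month has a mean of 3.5/6 = 0.58 of its final value, so averaging would still gain power at ρ = 0.10 but lose it at ρ = 0.5 or 0.7.

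**The case against.** The strongest reply is that these analyses are openly exploratory and that month 6 is a legitimate target: who benefits by the end of a six-month intervention is a fair question. On that target the regression is almost fully efficient, and the averaged interaction is a different quantity that wins clearly only if the effect is fairly stable. All of this stands. It limits the point to one of precision and consistency. It does not explain why month 6 is the sole target when the primary analysis is longitudinal, and the article gives no reason.

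A reader might infer more, in three ways.

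- **That the plan specifies a complete-case analysis biased by selective dropout.** The article does not say how missing month-6 values are handled in these regressions, and an article may leave that to the full protocol or analysis plan. Nothing in it shows that the patients with missing values are those who relapsed or became ill. Planned loss is 7.5%, and Results reports 6 of 144 (4.2%) removed so far, with 73 still in follow-up.
- **That precision is lost needlessly, by a factor of four.** That factor requires ρ = 0.10, all six months and a constant effect. With the two visits that Primary Analysis names, the factor is at most 1.83 over the correlations examined.
- **That the missing covariates make the analysis wrong.** The description is brief and may not list every covariate. Under stratified randomisation, leaving out AUDIT-10 or site costs some precision, which the article gives no figures to quantify. Clinic type is already in its own moderator model.

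**Conclusion.** The point holds as one of efficiency and consistency, of minor to moderate weight. The moderator model uses one of six monthly outcome windows and names fewer covariates than the primary model. Relative to an interaction averaged over follow-up, its variance is about 1.4 to 1.8 times as large with months 3 and 6, and about 2.0 to 4.1 times with all six months (ρ from 0.7 down to 0.10). In SE terms this is about 1.2 to 2.0 times. Only ρ = 0.10 is the plan's figure, and the ranges assume equal correlation between months and an effect constant over time. The primary comparison is untouched, and the documents do not support a finding of bias from missing month-6 data.

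**What to change.** Replace the separate month-6 regressions with moderator and moderator-by-arm terms in the primary longitudinal mixed model, using its covariates (site, clinic type, baseline abstinence, AUDIT-10) and all available monthly calendar follow-ups. Report the interaction averaged over follow-up, and give the month-6 interaction as a contrast from the same model by allowing the moderator-by-arm effect to vary with time. Keep the exploratory label.

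The cost is a change of wording; the data are already being collected, and the article reports recruitment as ongoing. The downside is that month 6 is no longer the sole target, and the averaged interaction says less if the effect builds or fades, which the month-6 contrast would show. If month 6 is deliberately the target, a sentence saying why, with the averaged interaction reported alongside, would meet most of the point.

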#### Randomization

This study uses a 1:1 block randomization plan for participant assignments to the intervention arm (n=149) versus no intervention arm (n=149), stratified by recruitment site (Wisconsin versus Michigan) and recruitment clinic type (general hepatology clinic versus multidisciplinary ALD clinic). The randomization tool within REDCap will be used for the randomization process, providing study arm assignments based on a predetermined allocation table programmed with the site and clinic type stratifications. To prepare for randomization, research staff will verify that informed consent has been signed and that all baseline surveys, including the TLFB, have been completed. During randomization, the research staff member opens REDCap, enters the current date, and initiates the REDCap randomization process. REDCap then assigns the participant to a study arm and notifies the staff member of the assignment outcome. This can take place either in-person during the clinic visit, over the phone, or in a virtual meeting. If the patient is assigned to the intervention group, study staff will assist them in downloading the Connections app and will guide them through its features. Participants using Connections are encouraged to create an alias name to protect their identity.

After randomization, a participant is considered enrolled in the study. They will remain in the study for 6 months following enrollment. During this time, they will complete monthly and quarterly surveys until the end of their study period. Participants may withdraw their consent at any time throughout the 6-month period after enrollment, at which time the study team will document their request and deactivate their account. The participant will not receive any further communication from the study.

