## Discussion

### Anticipated Findings

The study’s primary hypothesis anticipates that patients in the intervention group will have more abstinent days compared to patients in the usual-care group. Additionally, we anticipate the secondary hypotheses as outlined in Table 3. This includes patients in the intervention group showing greater improvement in secondary health outcomes compared to patients in the usual-care group, women in the intervention group benefiting more than men, patients in rural areas having greater improvements than patients living in nonrural areas, patients attending multidisciplinary ALD clinics receiving greater benefit from the intervention than those attending general hepatology clinics, and the association of increased Connections app use with overall greater improvements. Note that these secondary outcomes are exploratory.

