### Challenges

The implementation of a mHealth system presents several challenges. First, although mHealth approaches can increase overall accessibility to patients with ALD, they rely heavily on technology use and may be challenging for populations with low digital literacy. After enrollment, all components of the study require technology use, including completing monthly and quarterly surveys or exploring the CHESS Connections app if randomized to the intervention arm. Participants with low digital literacy may be less likely to check their emails or app notifications, which can lead to lower response rates, or they may be less likely to explore the intervention app. To address this, research staff have implemented frequent survey reminders to encourage study engagement. Second, while recruiting patients in-person during a clinic visit is preferred, it is time-consuming to enroll a patient from screening through randomization, particularly for patients to complete the baseline surveys, which could vary in length depending on the patient’s literacy skills and comfort level with technology. This often deters patients from completing enrollment during the clinic visit, leading to challenges such as missed virtual meetings to finish enrollment and patients that are lost-to-follow-up, even with multiple researcher follow-up attempts. Initially, patients used the MyCap app (Vanderbilt University)—a mobile, patient-facing version of REDCap—to complete baseline surveys and would download and create an account during onboarding. However, we learned that this lengthened the enrollment process substantially and have since eliminated the use of MyCap, opting for surveys to be sent through email or text instead. Another proposed challenge is the reliance on patient self-reporting of alcohol use, which introduces the possibility of underreporting or recall bias due to the 30-day recall period in the monthly TLFB surveys. Finally, while disparities for racial and ethnic minority patients are evident across the health care system, the higher rates of ALD among White patients parallels the patient panel in the 4 recruitment clinics in this study. This may limit the diversity of the study sample and decrease the ability to recruit any significant number of racial and ethnic minority patients into the study. To partially mitigate this concern, we will oversample patients from underrepresented groups during the qualitative portion of the study.

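### Subgroup effects are worked out only for significant interactions, a filter this trial is too small to apply without biasing the subgroup estimates it lets through

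*Protocol article*

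**What the plan says.** The Moderator Analysis section fits one linear regression per moderator, with abstinence days at 6 months as outcome, baseline abstinence days as covariate, and a moderator-by-arm interaction. It then sets the rule at issue: "Significant interaction effects will be decomposed to understand the differences between subgroups". The section's stated purpose is practical: "To guide future app refinements and deployment strategies, moderation analyses will assess which patient characteristics are associated with deriving greater benefit from using Connections". It also calls these analyses exploratory and hypothesis-generating, and the Anticipated Findings section repeats that they are exploratory. Table 3 nevertheless gives sex, rurality and clinic type directional hypotheses.

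Power and Sample Size covers the main comparison only: "With 7.5% loss to follow-up and a moderate effect size estimate of 0.3σ", "the planned sample size of 298 participants (149 per randomization group) will have power ≥80"%. It gives no power or detectable size for an interaction. The only subgroup share that can be derived is for clinic type. Of about 2361 patients in the recruitment pool, "it is expected that approximately 690 patients will be part of the multidisciplinary ALD clinics".

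**The concern.** An interaction estimate has a much larger standard error than the overall effect. If subgroup effects are worked out only when the interaction passes a significance test, the ones shown come from samples in which chance pushed the two subgroups apart. The favoured subgroup then looks better than it is and the other looks worse. A real but moderate difference usually fails the filter and is not broken down.

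These estimates are meant to inform who is offered the app. An app that helps both subgroups could look useless in one of them. The loss is greatest for small subgroups. The Challenges section warns that the patient panel may "decrease the ability to recruit any significant number of racial and ethnic minority patients into the study", yet race and ethnicity are on the same list and under the same rule.

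**Working it through.** **Inputs.** From the article: 298 randomised, 1:1 (Randomization: "This study uses a 1:1 block randomization plan for participant assignments"), 7.5% loss, overall effect 0.3σ, ρ = 0.10, and clinic-type share 690/2361 = 29.2% (if recruits mirror the pool). Assumed: two-sided 5%; ρ = 0.10 also serves as the baseline-to-6-month correlation r, with r = 0.5 as an alternative; other binary splits of 30–50%; true interactions of 0.15–0.60σ.

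**1. The plan's own figure.** Evaluable N = 298 × 0.925 = 275.65, or 137.8 per arm. For the mean of m visits, SE = √[(1 + (m − 1) × 0.10)/m] × √(2/137.8).
- m = 2: SE = 0.0894σ, 0.3/0.0894 = 3.36, power Φ(3.36 − 1.96) = 92%.
- m = 3: 97.6%. m = 6: 99.9%.
- m = 1: SE = 0.1205σ, power 70%.

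The stated power of at least 80% is therefore consistent with a repeated-measures analysis. The moderator regressions use one time point and do not get that gain.

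**2. Standard error of a binary interaction.** SE = √[4(1 − r²)/(N p(1 − p))].
- p = 0.50: √(3.96/68.91) = 0.240σ.
- p = 0.292: √(3.96/57.02) = 0.264σ.

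**3. Threshold and detectable size.** Smallest significant estimate = 1.96 × SE. True value for 80% power = (1.96 + 0.84) × SE.
- p = 0.50: 0.47σ and 0.67σ.
- p = 0.292: 0.52σ and 0.74σ.
- With r = 0.5 the thresholds are 0.41σ and 0.45σ.
- With p = 0.20 (assumed) and r = 0.10 the threshold is 0.59σ.

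**4. Power and overstatement of the interaction.** For a true interaction δ, overstatement is the mean absolute estimate given significance, divided by δ (truncated normal, r = 0.10).

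| True δ | Power, 50:50 | Overstated | Power, 29:71 | Overstated |
|---|---|---|---|---|
| 0.15σ | 9.6% | 3.9× | 8.8% | 4.2× |
| 0.30σ | 24% | 2.0× | 21% | 2.2× |
| 0.50σ | 55% | 1.3× | 48% | 1.4× |
| 0.60σ | 71% | 1.2× | 62% | 1.3× |

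**5. Overstatement of the subgroup benefit.** The share-weighted overall estimate (0.3σ) is uncorrelated with the interaction estimate. If E is the mean significant interaction and p the favoured subgroup's share, the favoured subgroup averages 0.3 + (1 − p)E and the other 0.3 − pE.
- 50:50, δ = 0.30σ: E = 2.04 × 0.30 = 0.612σ. Favoured: 0.606σ against a true 0.45σ (1.35×). Other: −0.006σ against a true 0.15σ.
- 29:71, δ = 0.15σ: E = 4.23 × 0.15 = 0.635σ. Favoured: 0.75σ against a true 0.406σ (1.85×). Other: 0.115σ against a true 0.256σ. Simulation of results significant in the true direction gives the same 1.85×. Counting the 6.5% of significant results with the wrong sign lowers it to about 1.7×.

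**6. One concrete case.** Suppose multidisciplinary-clinic patients truly benefit twice as much (0.46σ against 0.23σ, so δ = 0.23σ). The rule breaks this down about 14% of the time. The interaction then averages 2.8 times its true size, the multidisciplinary benefit about 1.6 times, and the general-clinic benefit about half.

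**The case against.** The strongest reply is that testing the interaction before probing subgroups is a conventional guard against spurious within-subgroup claims, that the article labels the work exploratory, and that the primary inference is untouched. Each part is true. The label restricts what may be claimed, but estimates chosen by a P-value filter stay biased, and hypothesis generation is better served by unfiltered estimates with intervals.

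The threshold is also sensitive to assumptions. It falls to 0.41–0.45σ if r = 0.5. The article mentions directional hypotheses, and a one-sided 5% test at 50:50 would need about 0.39σ (1.645 × 0.240). For a continuous moderator such as age it is about 0.24σ per SD (1.96 × 2/√275.65). These are fair limits on the figures and leave the direction of the bias unchanged.

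A reader might infer three stronger points that the article does not support:
- *Any reported subgroup benefit will be overstated two- to four-fold.* That factor belongs to the interaction contrast, and only for true interactions of about 0.15–0.30σ. The subgroup benefit is inflated by less. The article predicts that sex will moderate the effect to a large degree, and a large interaction would be inflated little.
- *Non-significant interactions will go unreported.* An interaction model is planned for every proposed moderator. Only the breakdown is conditional, and nothing says the interaction estimates will be withheld.
- *The sex hypothesis will be analysed within the intervention arm only.* The phrase "women in the intervention group benefiting more than men" is loose, but the specified model crosses the moderator with arm, so it targets the app's effect by sex.

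**Conclusion.** The point holds as a cheap improvement to an exploratory analysis. The article ties the subgroup breakdown to significance, in a design where a roughly balanced binary moderator must show about 0.47–0.52σ to pass and needs a true 0.67–0.74σ for 80% power. How much the filter distorts depends on the true interaction, which the article does not give. At 0.15–0.30σ the distortion is material for the contrast and for both subgroups. At 0.5–0.6σ it is modest. The figures rest on a two-sided 5% test, on recruits mirroring the pool for clinic type, on assumed splits for other moderators, and on ρ = 0.10 carrying over to the 6-month regression. The primary comparison is unaffected.

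**What to change.** Replace the sentence on decomposition with:

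> For every pre-named moderator, the interaction and the between-arm difference (Connections minus usual care) within each level will be reported with 95% CIs whatever the interaction P value; no subgroup conclusion will rest on significance alone.

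For continuous moderators, report the interaction slope with its CI.

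The cost is one sentence and one forest plot, with no new data or participants. The downside is that more wide intervals will be on display. Recruitment runs through 2027 and results are expected in 2028, so the change can be made well before analysis.
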